### Plan of statistical analysis for the secondary study parameters

3.2

Considering the standard clinical measurements on OCD severity, FA and secondary outcomes measures, reliable change indices (RCIs) [68] will be calculated for each individual participant to detect clinical relevant changes between all six assessment occasions (T0-T1-T2-T3-T4-T5), with the comparison between baseline (T0) and post-treatment (T4) as most relevant. RCI's will be calculated separately for each informant to collect meaningful information on differences between informants within one family. The RCI is a variable with three possible values: no reliable change, reliable deterioration and reliable improvement.

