### Participants

2.2

***Inclusion:*** Families are eligible to participate in this study if they meet all of the following criteria:(a)the child is referred to Levvel, Academic Center for Child and Adolescent Psychiatry, in Amsterdam between November 2023 and December 2024 for OCD treatment;(b)the child is between the age of 7–18 years old;(c)at time of baseline the child still meets the clinical cut-off of 16 or higher for OCD on the Child Yale-Brown Obsessive-Compulsive Scale (CY-BOCS) [31] and the child meets the DSM-5 criteria for OCD (as primary classification) as assessed with the Structured Clinical Interview for DSM-5 disorders (SCID-5 Junior);(d)psychiatric comorbidities of the child are included, provided that OCD is the primary treatment target;(e)parents report high levels of family accommodation (FA) at time of baseline (meeting the cut-off of 10 or higher on the Family Accommodation Scale Anxiety (FASA) [11]);(f)the child did not benefit from previous psychological treatment for OCD (he/she either followed 8 or more sessions of CBT or other psychotherapy), dropped out from treatment early or was unable/not motivated to receive individual treatment due to too high levels of anxiety or OCD;(g)children are allowed to use medication or selective serotonin reuptake inhibitors (SSRI's) for OCD symptoms, provided that the medication regime has been stable 4 weeks prior to participation and is expected to remain unchanged during participation.

***Exclusion:*** families meeting any of the following criteria will be excluded:(a)the child needs inpatient treatment;(b)parents are not willing to participate;(c)the child displays acute suicidality;(d)the child displays psychotic symptoms;(e)parents have insufficient mastery of the Dutch language;(f)parents or child have an estimated IQ below 75. IQ will not be tested during screening for this study, but a clinical judgement is made by the clinician during screening or intake, based on school career and medical file of the child.

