### Secondary outcome measures

2.9

*Children's Yale-Brown Obsessive-Compulsive Scale*. OCD symptoms and OCD severity will be assessed with the Children's Yale-Brown Obsessive-Compulsive Scale (CY-BOCS) [31], a clinician rated semi-structured interview based on a combined parent and child-report and clinical evaluation. The CY-BOCS consists of a symptom checklist and a severity scale. The symptom checklist assesses current and past obsessive and compulsive experiences (indicated with ‘yes’ or ‘no’). The severity scale consists of 5 items on obsession severity and 5 items on compulsion severity, rated on a scale from 0 to 4. The total score is the sum of the obsessive and compulsive scale (0–40). A higher score indicates more severe OCD symptomatology. The CY-BOCS has good reliability (*α* = 0.87) and construct validity [38]. Comparable properties have been found for the Dutch translation of the CY-BOCS [39].

*Family Accommodation Scale-Anxiety.* The Family Accommodation Scale – Anxiety (FASA) [11] is a parent report measure and comprises 9 items rated on a Likert scale from 0 (never) to 4 (daily) that add up to the total accommodation score. Four additional items, rated from 0 (no) to 4 (extreme), assess the distress and consequences of family accommodation. The FASA-CR is a child-rated version with comparable items. The FASA (*α* = 0.87) and FASA-CR (*α* = 0.79) have shown good test-retest reliability in English speaking samples [40]. The validation of the Dutch version of the FASA and FASA-CR is currently in progress in a parallel study.

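### The reliable change index is given the task of detecting clinically relevant change, which it cannot do, and the FASA reliability figures it may need are labelled inconsistently

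*Protocol article*

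**What the plan says.** Section 3.2 (plan for the secondary study parameters) states that "reliable change indices (RCIs) [68] will be calculated for each individual participant to detect clinical relevant changes between all six assessment occasions", "with the comparison between baseline (T0) and post-treatment (T4) as most relevant". RCIs are computed separately for each informant. The section then defines the result: "The RCI is a variable with three possible values: no reliable change, reliable deterioration and reliable improvement". It attaches no clinical criterion to any of these values.

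Clinical thresholds do appear elsewhere. Section 2.2 (Participants) requires that "at time of baseline the child still meets the clinical cut-off of 16 or higher for OCD" on the CY-BOCS, and that parents score 10 or more on the FASA. Both are entry criteria, and neither is linked to the RCI.

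Section 2.9 (Secondary outcome measures) gives α = 0.87 for the FASA and α = 0.79 for the FASA-CR, and says that the two scales "have shown good test-retest reliability in English speaking samples". For the CY-BOCS it also gives α = 0.87, but calls this only reliability. On the Dutch scales it says: "The validation of the Dutch version of the FASA and FASA-CR is currently in progress in a parallel study".

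**The concern.** There are two separate problems.

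The first is one of meaning. The RCI compares a change with the change that measurement error alone would produce. It does not ask whether the change matters, or whether the child has left the clinical range. Section 3.2 announces clinical relevance and then defines an output that cannot show it. RCIs are the only analysis that section 3.2 names for these scales, so the label will govern how the CY-BOCS and FASA results are read.

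The second concerns an input. The RCI threshold depends on a reliability coefficient. For scores weeks or months apart, that should be a test-retest coefficient. Alpha normally denotes internal consistency, which does not capture fluctuation between occasions. Section 2.9 joins the symbol for one to the name of the other. If an internal-consistency value that exceeds the retest value were used, the threshold would be too low and too many unchanged respondents would be flagged.

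**Working it through.** The article states no RCI threshold, SD or expected number of changed respondents, so there is no figure of its own to reproduce. The standard form of the RCI is assumed, with normal errors and equal SDs on both occasions.

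**Step 1: does a clinical criterion enter the RCI?** A change is reliable if |difference| > 1.96·SD·√(2(1−r)). The only inputs are SD and r, and neither the cut-off of 16 nor that of 10 appears. For the CY-BOCS with r = 0.87, the multiplier is 1.96·√(2·0.13) = 1.00. With an assumed SD of 5 to 9 points (the article gives none), the threshold is about 5 to 9 points on a scale of 0 to 40. Two illustrations at SD = 6 (threshold 6.0):

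- A child who goes from 30 to 22 falls by 8 points. This is reliable improvement, but the score is still 6 points above the cut-off.
- A child who goes from 18 to 14 falls by 4 points. This crosses the cut-off but is not reliable.

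The two criteria answer different questions, and neither implies the other.

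**Step 2: what if the FASA coefficient is too high for this use?** Let r_used be the coefficient in the formula and r_tt the true retest reliability. For a respondent with no true change,

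flag rate = 2·[1 − Φ(1.96·√((1 − r_used)/(1 − r_tt)))].

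FASA, r_used = 0.87 (threshold 1.00 SD); r_tt is assumed:

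| r_tt | Threshold it would call for | Argument of Φ | Flag rate, both directions | Per 25 respondents |
|---|---|---|---|---|
| 0.90 | 0.88 SD | 1.96·√(0.13/0.10) = 2.23 | 2.5% | 0.6 |
| 0.87 | 1.00 SD | 1.96 | 5.0% | 1.3 |
| 0.80 | 1.24 SD | 1.96·√(0.13/0.20) = 1.58 | 11.4% | 2.9 |
| 0.70 | 1.52 SD | 1.96·√(0.13/0.30) = 1.29 | 19.7% | 4.9 |

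False improvement is half of each rate, for example 5.7% at 0.80 and about 9.9% at 0.70.

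FASA-CR, r_used = 0.79 (threshold 1.27 SD): 4.5% at r_tt = 0.80, 5.0% at 0.79 and 10.1% at 0.70.

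Inflation therefore needs r_tt to lie below the coefficient used. Otherwise the rate is nominal or lower.

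**The case against.** The strongest reply to the first problem is that the three outcome values are already worded as reliability, so the eventual tables may carry the right label. That limits the damage but does not remove the contradiction. The sentence that gives the purpose still promises clinical relevance, and nothing in section 3.2 delivers it.

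On the second problem the reply is stronger. The article never says that 0.87 or 0.79 will enter the RCI. The choice of coefficient and SD may sit in the full protocol or analysis plan, and the parallel Dutch validation study may be the intended source. Nor can one tell from the article whether the symbol or the label is wrong. If the values are retest coefficients printed under the wrong symbol, there is no inflation. What stands is the inconsistency itself and a conditional risk.

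A reader might go further and infer that too many families will be called changed. The documents do not support that. The effect is conditional, and the unit is the respondent, because RCIs are computed per informant.

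A reader might also infer that six occasions give 15 pairs, and hence a 37% chance of at least one false flag in an unchanged respondent even with the right coefficient. That figure (36.6%, from the studentized range of six independent normal scores) fits only the four instruments that Table 2 schedules at all six occasions: CY-BOCS severity, FASA, FASA-CR and CD-POC. The SCARED and CDI-2 have four occasions (6 pairs), and the CBCL, TRF, YSR and EQ-5D forms have three (3 pairs). More importantly, no rule counts a flag in any pair as response, and T0 to T4 is already singled out. Multiplicity is therefore not a fault in its own right here.

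**Conclusion.** The first problem holds as stated. Section 3.2 assigns the RCI a purpose that its own output definition does not meet, and a child could be described as clinically relevantly changed on the CY-BOCS with a score still at or above 16. The documents do not allow the number of such children to be estimated.

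The second problem holds as an inconsistency with a conditional consequence. If the printed FASA value is internal consistency, if it is used in the RCI, and if retest reliability is 0.70 to 0.80, the nominal 5% false-change rate becomes about 20% to 11%. That is roughly 5 to 3 per 25 unchanged respondents instead of 1.3. At a retest reliability of 0.87 or more there is no inflation. The mislabelling concerns the FASA and FASA-CR only, not the CY-BOCS.

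Both problems concern secondary outcomes. The primary single-case analysis of the frequent measure is unaffected.

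**What to change.** - In section 3.2, describe the RCI result as *reliable change*. Reserve *clinically relevant* for reliable improvement that also crosses the protocol's own cut-off: CY-BOCS below 16, or FASA below 10. For scales with no cut-off in the protocol, including the FASA-CR, report reliable change only.
- In section 2.9, correct either the symbol or the label for the FASA and FASA-CR.
- State which coefficient and SD enter the RCI, and make the coefficient a test-retest one, for example from the parallel Dutch validation study if it provides one.
- Keep T0 to T4 as the headline pair and present the other pairs as descriptive.

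This changes wording and analysis only, and no family has to provide further data. The article reports 9 families enrolled as of October 2024 and data collection projected to be complete in 2025, so the definitions should be fixed before the RCI results are examined. The cost is that fewer respondents will be labelled clinically relevantly improved.

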## Abstract

**Background:**

Pediatric obsessive-compulsive disorder (OCD) is a severely impairing disorder, associated with high levels of family accommodation (FA). Approximately 40 % of youth do not benefit from first-line treatment options (cognitive behavioral therapy or pharmacotherapy). Supportive Parenting for Anxious Childhood Emotions (SPACE) is a parent-based treatment, teaching parents to reduce FA and increase supportive parenting, thereby aiming to improve the child's OCD. This article presents the protocol of a multiple baseline single-case experimental design (SCED) study to test the efficacy of SPACE in reducing OCD severity and FA in youth with OCD.

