Additionally to the SCED design, comprehensive standard clinical assessments are carried out to assess for pre-, during-, post- and follow-up differences at the following six timepoints: T0: baseline assessment during intake; T1: at the end of the baseline phase (four, six or eight weeks after T0), before treatment starts; T2: after four treatment sessions (on average four weeks after T1); T3: after eight treatment sessions (on average eight weeks after T1); T4: after all 12 treatment sessions are completed (on average 12 weeks after T1); T5: follow-up assessment, six months after T0. Moreover, every treatment session parents report about their well-being and working alliance and the therapist report about illness severity and improvement. An overview of all assessments is provided in Fig. 1 and Table 1.

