### Primary outcome measure

2.8

*Frequent measure on OCD and FA.* The frequent measure is a brief 4-item questionnaire on the level and time spent on OCD and FA (see Table 3). The questions are developed in collaboration with experience experts from patient organizations and families who previously received therapy for their child's OCD. Each item is rated on a 11-point scale (0–10). Both parents and the child complete the questions independently of each other.

**Table 3 tbl3:** Frequent brief assessment questions on OCD and FA for parents and children.

	Question	Scale
OCD questions parents		
1	To what extent did your child experienced obsessions and compulsions today (including the night)?	0 (*not at all*) to 10 (*to the fullest extent*)
2	How much time did your child spend on obsessions and compulsions today (including the night)?	*0 min* to *more than 8 h*
FA questions parents		
3	To what extent did you accommodate to the obsessions and compulsions of your child today (including the night)?	0 (*not at all*) to 10 (*to the fullest extent*)
4	How much time did you spent accommodating to the obsessions and compulsions of your child today (including the night)?	*0 min* to *more than 8 h*
OCD questions child		
1	To what extent did you experienced obsessions and compulsions today (including the night)?	0 (*not at all*) to 10 (*to the fullest extent*)
2	How much time did you spend on obsessions and compulsions today (including the night)?	*0 min* to *more than 8 h*
FA questions child		
3	To what extent did your parents accommodate to your obsessions and compulsions today (including the night)?	0 (*not at all*) to 10 (*to the fullest extent*)
4	How much time did your parents spent accommodating to your obsessions and compulsions today (including the night)?	*0 min* to *more than 8 h*

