### Plan of statistical analysis for the SCED primary study parameters

3.1

In this study, the main objective is to explore the efficacy of SPACE. The primary analysis focuses on the change in the frequent measure on OCD and FA between baseline phase (A) and treatment phase (B1+B2). First, individual participants data will be separately systematically visually analyzed [61]. Next, individual data will and modelled using a generalized least squares (GLS) approach (assuming autocorrelation) [62]. To test the treatment effect on group level, a multilevel modelling approach [63] based on the examples of Shadish and colleagues (2013) [64] and Moeyaert and colleagues [63,65,66] will be used. Data from all individual participants will be included in the multilevel model and structured across a hierarchical three-level structure. Level 1 represents the frequent measurement occasions, with measures being nested within each participant. Level 2 represents the individual participants (mothers, fathers and children), with family members being nested in a family unit. Level 3 represents the family units (e.g. members of one family) included in this study. Adding time-variant predictors (the number of measurement occasion to model general time trend, a dummy-coded variable (0–1) representing the phase and an interaction term between these two) at Level 1 allows to explore for a shift in level of OCD and FA at the start of the treatment phase and the shift in trend during the treatment phase [65]. Multiple plausible multilevel models will be estimated to enhance conclusions about the treatment effect [63]. For these analyses a significance level of 0.05 is used.

Exploratory, we expect the greatest shift in OCD severity and FA level in phase B2 when parents implement their plan to reduce FA. By starting phase B2 directly after implementation of the plan we aim to explore the immediate effect of the implementation and shift in OCD and FA level during the second half of the treatment. For this purpose, an additional time predictor at Level 1 will be added to estimate shift in level and shift in trend for phase B2.

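### Section 3.2 analyses the CY-BOCS and FASA only as individual three-category RCIs led by T0–T4, so it plans no group estimate of change and its lead contrast mixes untreated baseline with treatment

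*Protocol article*

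**What the plan says.** The abstract of the protocol article sets the aim: "to test the efficacy of SPACE in reducing OCD severity and FA in youth with OCD". Section 2.1 schedules six clinical assessments, T0 to T5, and says why: "comprehensive standard clinical assessments are carried out to assess for pre-, during-, post- and follow-up differences". T0 is at intake, T1 closes the untreated baseline, T4 follows the twelfth session, and T5 is six months after T0.

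Section 3.2 covers how these scores are analysed. In it, "reliable change indices (RCIs) [68] will be calculated for each individual participant", between all six occasions and separately by informant, "with the comparison between baseline (T0) and post-treatment (T4) as most relevant". The coding is fixed: "The RCI is a variable with three possible values: no reliable change, reliable deterioration and reliable improvement". No mean change, interval, group model or test is named.

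The individual GLS models and the three-level model in section 3.1 are described for the frequent four-item measure. The same holds for the error rate in that section: "For these analyses a significance level of 0.05 is used".

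**The concern.** The clinical scores are continuous and are measured on two occasions before treatment and four during or after it. Reducing each pair of scores to three labels shows who crossed a threshold. It does not show how far the group moved or how precisely that is known, although the assessments exist to show differences over time.

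The lead contrast adds a second problem. T0 comes before the untreated baseline, so change from T0 to T4 contains both waiting and treatment. Section 2.2 requires minimum CY-BOCS and FASA scores at baseline, and section 2.1 calls T0 the baseline assessment. If those are the same scores, families were selected partly for being high at T0, and some fall afterwards is expected without any treatment effect.

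The group-level test of efficacy rests on a new measure. Of its items the article says "The questions are developed in collaboration with experience experts from patient organizations", and it reports no psychometric evidence for them. The CY-BOCS is an established clinician-rated scale and the natural corroboration, yet as planned it yields only counts of improved, unchanged and worse.

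**Working it through.** **Inputs from the protocol article.** Baseline of 4, 6 or 8 weeks (2.4). Treatment of about 12 weeks (2.3). 72 frequent assessments at three a week (2.7), which is 72/3 = 24 weeks in all. Stated reliability of 0.87 for the CY-BOCS and the FASA (2.9). 25 families with 16–25% dropout (2.1), leaving 25 × 0.84 = 21 or 25 × 0.75 = 18.75, taken as 19.

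**Assumptions, because the article gives no SD, correlation or effect size for these scores.** Score SD and SD of change of 5–8 points; T0–T4 correlation ρ of 0.3–0.7; two-sided 5%. There is no power figure in the article to reproduce. The number 25 is justified by cited minimum case numbers and expected dropout.

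**1. What T0–T4 spans.** Its length is 4 + 12 = 16, 6 + 12 = 18 or 8 + 12 = 20 weeks, depending on the randomised baseline. The untreated share is 4/16 = 25%, 6/18 = 33% or 8/20 = 40%. The other intervals are also unequal: T0–T1 is 4, 6 or 8 weeks, T1–T4 about 12, and T4–T5 is 24 − 16 = 8, 24 − 18 = 6 or 24 − 20 = 4.

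**2. The RCI threshold.** 1.96 × √(2 × (1 − 0.87)) = 1.96 × √0.26 = 1.00 SD, or 5–8 points for an SD of 5–8.

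**3. What the three labels retain.** For a true mean improvement m in SD units, the SD of change is s = √(2(1 − ρ)) and the proportion improved is 1 − Φ((1.00 − m)/s).
- m = 0.8, ρ = 0.5: s = 1, giving 42% improved, 54% no reliable change and 4% deteriorated.
- m = 0.5, ρ = 0.5: 31% improved and 62% no reliable change. Over ρ = 0.3–0.7, 56–71% show no reliable change.

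With 19 families and ρ = 0.5, those two effects differ by 0.42 × 19 − 0.31 × 19 = 8.0 − 5.9, or about two families labelled improved. The counts alone say little about size.

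**4. What a group mean would give.** The 95% CI half-width is t(0.975, n − 1)/√n in SD of change.

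| Families | Half-width (SD of change) | Points, SD of change 5–8 |
|---|---|---|
| 25 | 0.41 | 2.1–3.3 |
| 21 | 0.46 | 2.3–3.6 |
| 19 | 0.48 | 2.4–3.9 |

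**5. Illustration of information lost.** Take the score SD equal to the SD of change. Compare the power of a paired t-test of mean change with that of an exact sign test of RCI improvers against deteriorators.

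| True change (SD of change) | n = 19: t-test, sign test | n = 25: t-test, sign test |
|---|---|---|
| 0.6 | 0.70, 0.39 | 0.82, 0.56 |
| 0.8 | 0.91, 0.67 | 0.97, 0.84 |
| 1.0 | 0.98, 0.88 | 1.00, 0.97 |

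The gap is wide at moderate effects and small at large ones. The article plans no sign test, so this shows only the direction and rough size of the loss.

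**The case against.** The strongest reply is that this is a single-case design. Efficacy on OCD severity and accommodation is tested at group level in section 3.1, on densely repeated ratings with randomised baseline lengths. An uncontrolled before–after mean is weaker evidence than that. RCIs are a proper measure of individual clinical relevance, and each one tests a participant's change against measurement error. This stands: the RCIs should stay, and any added model should be supportive only.

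A reader might infer more than the article supports.
- **That the RCIs cannot separate waiting from treatment.** They are planned between all six occasions, so T0–T1 and T1–T4 are available for each individual. What is missing is a group estimate, and the emphasis falls on the contrast that mixes the two periods.
- **That the CY-BOCS and FASA are both validated outcomes.** Sections 2.9 and 4.1 say the Dutch FASA is not yet validated. Comparable Dutch properties are reported only for the CY-BOCS.
- **That the trial has no estimate or test of OCD severity or accommodation.** It has both, on the frequent measure.

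The article is also a condensed account, and a fuller analysis plan may add group summaries. That limits the point but does not remove it, because section 3.2 itself chooses the method, the coding and the lead comparison.

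**Conclusion.** The point holds in a limited form. As section 3.2 stands, the CY-BOCS and FASA yield individual categories and no group estimate of change with an interval. The comparison given most weight includes 25–40% untreated time and starts from a score open to regression to the mean. This does not undermine the primary analysis. It weakens the corroboration that the clinical scales could give, the CY-BOCS above all.

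A mean change could be estimated to within about 0.41–0.48 SD of change at the planned size after dropout. The point-scale figures, the category percentages and the power comparison rest on assumed SDs, correlations and effects and are illustrative. The regression-to-the-mean argument rests on reading the eligibility scores as the T0 scores. Sections 2.1 and 2.2 imply this but do not state it outright.

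**What to change.** Keep the RCIs as the individual-level description, and name T1–T4 rather than T0–T4 as the lead treatment contrast.

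Add one linear mixed model for CY-BOCS severity and one for parent-reported FASA over T0–T5. Include a random family effect, with informant nested in family where both parents complete the FASA. Because the intervals differ in length, occasion as a factor alone would not compare waiting with treatment like for like. Either use actual time in weeks with separate slopes for baseline, treatment and follow-up, or report the T0–T1, T1–T4 and T4–T5 changes per week as well as in total. Give each a 95% CI and label them supportive secondary results. State that T0–T1 may itself contain regression to the mean, and note the unfinished Dutch validation beside the FASA result.

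The cost is two further models on data already scheduled, with no change to conduct. Nine families were enrolled at submission in October 2024, with data collection projected to finish in 2025. The addition should be written down and dated before these data are analysed.

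### The reliable change analysis gives priority to T0–T4, an interval that contains the whole untreated baseline phase, although a pre-treatment T1 score exists for the main instruments

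*Protocol article*

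**What the plan says.** Section 3.2 plans an RCI for each participant and informant on the standard clinical measures. The indices are calculated "between all six assessment occasions (T0-T1-T2-T3-T4-T5"), and one pair is then ranked above the others: "with the comparison between baseline (T0) and post-treatment (T4) as most relevant". The outcome is categorical: "The RCI is a variable with three possible values: no reliable change, reliable deterioration and reliable improvement".

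Section 2.1 fixes the timing:
- "T0: baseline assessment during intake"
- "T1: at the end of the baseline phase (four, six or eight weeks after T0), before treatment starts"
- "T4: after all 12 treatment sessions are completed (on average 12 weeks after T1")

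The same section describes phase A as a phase without treatment, and section 2.4 assigns its length at random.

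Section 2.2 sets two score-based entry criteria. For the CY-BOCS, "at time of baseline the child still meets the clinical cut-off of 16 or higher for OCD". For accommodation, "parents report high levels of family accommodation (FA) at time of baseline", with a FASA cut-off of 10.

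Table 2 schedules CY-BOCS severity, FASA, FASA-CR, CD-POC, SCARED and CDI-2 at both T0 and T1. CBCL, TRF, YSR, EQ-5D and EQ-5D-Y are scheduled at T0, T4 and T5 only.

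**The concern.** A baseline to post-treatment improvement rate will naturally be read as describing what happened under SPACE. With T0 as the starting point, it also covers everything that happened in the four to eight weeks before the first session. How much untreated time is included differs between families, because baseline length is randomised. T0 is also the assessment at which families had to score above two cut-offs, so some fall at the next measurement is expected without any real change.

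T1 avoids both problems. It is taken after the untreated phase and before treatment, and entry does not depend on it. It exists for the two instruments that carry the entry cut-offs. At stake is how many children are described as reliably improved on the CY-BOCS and FASA in the contrast that the article tells the reader to look at first.

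**Working it through.** **Timeline, starting from the article's own figures.** Section 2.7 gives three brief assessments a week, 12–24 in the baseline phase and 36 in the treatment phase. At three a week, 4, 6 and 8 weeks give 12, 18 and 24 assessments, and 12 weeks give 36. The article's figures are reproduced, which confirms the phase lengths.

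Untreated share of T0–T4 = baseline weeks / (baseline weeks + 12):
- 4 / 16 = 25%
- 6 / 18 = 33%
- 8 / 20 = 40%

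For T1–T4 the interval is about 12 weeks and the share is zero.

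**Size of the effect on the RCI.** The article gives a CY-BOCS reliability of 0.87 (section 2.9) and the entry cut-off of 16. It gives no population mean, SD, retest correlation, untreated drift or RCI cut-off. Assumed here: mean 20–22 and SD 6–7 among referred children, retest correlation 0.87 or 0.75, an RCI multiplier of 1.96, and no treatment effect.

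RCI threshold = 1.96 × SD × √(2 × (1 − 0.87)):
- SD 6: 1.96 × 6 × 0.510 = 6.0 points
- SD 7: 1.96 × 7 × 0.510 = 7.0 points

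For T1–T4, with no change after T1, the false improvement rate follows directly. At retest 0.87 it is 1 − Φ(1.96) = 2.5%. At retest 0.75 the SD of the difference is SD × √(2 × 0.25) = 0.707 SD and the threshold is 0.999 SD, so the rate is 1 − Φ(1.41) = 7.9%.

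For T0–T4, scores were simulated as a normal true score plus error (2 million draws per setting), keeping only those with T0 of at least 16. Drift is a fall between T0 and T1. The ranges run over the assumed means and SDs.

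| Retest correlation | Mean T0–T4 fall from selection alone | False improvement T0–T4, no drift | Drift 2 points | Drift 3 points | False improvement T1–T4 |
|---|---|---|---|---|---|
| 0.87 | 0.2–0.4 points | 2.8–3.1% | 9–11% | 15–19% | 2.5% |
| 0.75 | 0.4–0.8 points | 9.0–10.0% | 18–21% | 24–28% | 7.8–7.9% |

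The entry cut-off alone adds 2.8 − 2.5 = 0.3 points at the lower end and about 10 − 8 = 2 percentage points at the upper end. Drift accounts for most of the rest.

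If all 25 families reached T4, 9–28% would be about 2 to 7 families (0.09 × 25 = 2.3; 0.28 × 25 = 7.0), against about 1 to 2 for T1–T4 (0.025 × 25 = 0.6; 0.08 × 25 = 2.0).

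**Wider assumptions.** With means 18–25, SD 5–7 and retest 0.87 or 0.70, selection alone lowers the CY-BOCS mean by 0.05–1.3 points. A 2-point drift gives 9–15% false improvement at 0.87 and 19–28% at 0.70, against 2.5% and about 10% for T1–T4. For the FASA (assumed mean 12–20, SD 7, reliability 0.87 for the threshold), selection alone lowers the mean by 0.1–1.3 points.

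**The case against.** The strongest reply is that little is lost. RCIs are planned between all six occasions, so T0–T1 and T1–T4 will be calculated for every instrument with a T1 score. Efficacy is tested in section 3.1, which compares phase A with B1+B2 on the frequent measure and models level and trend. The baseline phase does its control work there. This stands. A reader might infer that the plan throws away its own control, or that the trial's main responder result is biased. The article supports neither: the RCI analysis is secondary, and section 3.2 speaks of clinically relevant change, not of response to treatment.

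A reader might also make regression to the mean the main issue. The calculation does not bear this out, since selection alone adds at most about 2 percentage points. That T0 and the eligibility score are the same administration is likely, because both are placed at baseline or intake, but it is not stated outright.

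Nor can it be said that the problem falls on the trial's only validated OCD and accommodation measures. Sections 2.9 and 4.1 report that validation of the Dutch FASA and FASA-CR is still under way.

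The drift of 2–3 points is an assumption. The background section describes untreated OCD as chronic, and entry requires a stable medication regime, so large spontaneous improvement is not to be presumed. This limits confidence in the size but not in the direction of the argument: T0–T4 cannot separate whatever change does occur before treatment.

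Finally, T0–T4 is the only pre–post interval available for all the T0–T5 outcome instruments and is a valid description of total change since intake. That is a fair reason to report it, but not to rank it first where T1 exists.

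**Conclusion.** The point holds as a matter of priority among contrasts that are already planned. The RCI comparison named most relevant contains the whole untreated phase (25–40% of its length, varying by randomised allocation) and starts from the intake assessment at which the entry cut-offs apply. Change before treatment can therefore be counted as reliable improvement from baseline to post-treatment.

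The timeline part rests on the article alone. The size does not, since every misclassification rate depends on the assumed mean, SD, retest correlation, 1.96 multiplier and drift. If there is no untreated drift, the practical difference is small. If CY-BOCS scores fall 2–3 points before T1, the false improvement rate is several times higher for T0–T4 than for T1–T4 at retest 0.87, and two to four times higher at 0.75.

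T1–T4 is protected only against change before T1. Natural improvement that continues during the 12 treatment weeks would still enter it, which is why T0–T1 belongs beside it.

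**What to change.** In section 3.2, name T1–T4 as the most relevant RCI comparison for every instrument measured at T1: CY-BOCS severity, FASA, FASA-CR, CD-POC, SCARED and CDI-2. Present T0–T1 beside it as the untreated change, noting that its length is four, six or eight weeks. Keep T0–T4 as the pre–post contrast for CBCL, TRF, YSR, EQ-5D and EQ-5D-Y, labelled as including the untreated phase.

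No new data, visits or participants are needed; the change is one of wording and should be made before results are examined. It has two costs: the reported improvement rate may be somewhat less favourable, and the leading contrast will differ between instruments, which the tables must make clear.
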